
#### Quantitative assessment of patient activation within clinical encounters

Differences in the number of patient activation utterances, ACP topics discussed, and length of time discussed will be compared between groups using mixed effects models as above with a random intercept for physician. Clinician race/ethnicity, and gender will be included as covariates as these variables are associated with doctor-patient communication [41]. We will also obtain the number of utterances that may signify clinician contamination (knowledge of study arm) to control for these findings.

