Functional status	Activities of Daily Living (ADL) and Instrumental Activities of Daily Living (IADL)	15	Morbidity/mortality correlation [51, 52]		X			
Self-rated health status	In general how would you rate your health? (5-pt Likert)	1	Correlation with global health, spearman’s rho = -63, and mortality [53]	X				
Self-rated quality of life	In general, how would you rate your overall quality of life in the past week (5-pt Likert)	1	Test-retest coefficient = 0.81 [54]	X				
Comorbid illness	Determined by ICD-9 codes (chart)	0	Mortality c-stat: [23]		X			
	Charlson comorbidity score [24]		Charlson = 0.704					
	Elixhauser comorbidity score [55]		Elixhauser = 0.793					
Social support	Modified Medical Outcomes Study Social Support (mMOS-SS)	11	Cronbach’s α = 0.88-.93 [56]		X			
Religion/spirituality	Self-reported extent of how spiritual/religious (5-pt Likert) and role play in decision-making.	4	Spirituality associated with quality of life. Religiosity associated with wanting all measures to extend life [57]		X			
Prior ACP experience	Prior ACP experiences (for example, Ever had to make life threatening medical decisions?”) [12]	5			X			
Major life changes	For example, “In the past 6 months, have you or someone close to you been faced with a serious medical problem or diagnosis?”	4						X
	Mediator variables^a^ (also measured as Outcome Variables)							
Baseline knowledge	Knowledge subscales of the ACP Engagement Survey.	6	Cronbach’s α = 0.84 (0.76-0.90), ICC = 0.70 (0.50-0.82) [15]		X			
Baseline self-efficacy	Self-efficacy subscales of the ACP Engagement Survey.	6	Cronbach’s α = 0.83 (0.75-0.89), ICC = 0.60 (0.41-0.76) [15]		X			
Baseline readiness	Readiness subscales of the ACP Engagement Survey.	10	Cronbach’s α = 0.92 (0.88-0.95), ICC = 0.60 (0.53-0.81) [15]		X			
Baseline barriers	Checkbox of 13 common barriers	13	Associated with ACP [25]		X			
Baseline attitudes	Processes of Change for ACP [16]	34	Responsive to an ACP intervention [15]		X			
Desired role in decision-making	Control Preference Scale (CPS) [58]	2	Correlation between preferred and actual role in decision-making [59–61]		X			X
	Primary Outcome Variables							
Full process of ACP	ACP Engagement Survey: Process Measures of knowledge, contemplation, self-efficacy, readiness	116	Process Measures: Cronbach’s α = 0.94 (0.91-0.96), ICC = 0.70 (0.54-0.82) [15]		X	X	X	X
	Action Measures: completion of advance directives, discussions		Action Measures: ICC = 0.87 (0.79-0.92) [15]					

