The sample size of 350 Veterans will also allow adequate power to assess interactions based on potential moderating variables (race/ethnicity, literacy, gender) for our outcomes. We also anticipate very low intra-clinician correlations due to clustering or contamination; randomization is at the patient level not at the clinician level, and intra-clinician correlation values for patient attitudes and knowledge are typically quite low even in physician-level cluster randomized trials (for example, 0.015) [38]. Furthermore, as we have a potential pool of 115 clinicians, most clinicians will care for no more than one to three eligible Veterans and thus, there will be negligible loss of effective sample size accounting for clustering and contamination.

In exploratory analysis to corroborate Veteran reports of activation, we will attempt to recruit 144 surrogates (72 in each arm) anticipating that 20 % of Veterans will not have identified a surrogate based on pilot data, 15 % of Veterans will be lost to follow-up, and 30 % of surrogates will refuse. For patient activation within clinical encounters, we will attempt to audio-record 200 Veterans (100 in each group) to account for potential 25 % of enrolled Veteran and 25 % clinician refusal rates. For input about implementation, we anticipate recruiting 175 Veterans in the PREPARE arm (accounting for a 15 % drop-out at 6 months) and 72 of PREPARE arm Veteran’s surrogates.

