### Data analysis

#### RCT efficacy analysis

Our primary analyses will compare advance directive completion rates and change in engagement in the five ACP behaviors (see Primary outcome section) using behavior change measure scores on a 5-point Likert scale (analyzed as average Likert scores and total scores of 57 to 285) and action measure scores using yes and no responses (scores 0 to 25) from baseline to 1 week, and 3, and 6 months between study arms. We first will use means, medians, and ranges to describe continuous variables, and we will use proportions to describe categorical and dichotomous variables. Baseline comparability of the two groups will then be assessed using t-tests for continuous variables and chi-square tests for proportions. To examine the outcomes between the two study arms longitudinally, we will use mixed effects linear, Poisson, or negative binomial regression for continuous outcome measures and mixed effects logistic regression for dichotomous measures. The mixed effects models will include a random effect for subjects and fixed effects for the primary modeling terms of time, study arm, and an interaction term of study arm and time. We will treat the time variable in three different ways: (i) our first model will encode the time variable as a dummy variable for baseline versus the post-intervention time points; (ii) we will next model time in a continuous linear fashion; (iii) we will lastly consider an arbitrary time course by treating time as a categorical factor variable. We will also adjust for the randomization blocking factors of health literacy (limited versus adequate) and race (white versus non-white) [39] and for any predictor variables that differ between study arms at baseline. We will also include random physician intercepts to account for nesting of patients within physicians. We will consider including random effects for the primary modeling terms of time, study arm, and their interaction. Modeling decisions (for example, which mean structure to use and which random effects to include) will be based on comparing values of the Akaike Information Criterion. Models will be fit using the xt routines in Stata. Mediation analyses will use Stata’s mediation package, which allows estimation of the average causal mediation effect using a potential outcomes framework with either continuous or binary outcomes and allows for sensitivity analyses with respect to violation of the sequential ignorability assumption [40]. Moderating variables will be tested with interaction terms.

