There have been a few logistic challenges to date. Although we attempt to schedule Veteran’s baseline appointment and randomization 1 to 3 weeks prior to their most proximate primary care appointment, this, at times, has been difficult to implement for various reasons. For example, some Veterans reschedule their baseline interview resulting in the intervention occurring within a few days before their clinic visit. Other Veterans or the clinic will cancel a primary care appointment after the baseline interview has occurred resulting in a time frame beyond the three-week ideal. We will adjust for these varying time frames from exposure to the intervention in our analyses. In addition, because the audio-recording occurs at the primary care visit and because several primary outcomes of the study would occur at the primary care visit, we decided to make the primary care visit the date from which all follow-up interviews would be calculated. Because follow-up of the 1-week, 3-month and 6-month interviews within defined time frames was proving challenging, we decided to allow a range of dates that were acceptable. For instance, if a primary care appointment is rescheduled is outside of the ideal 1-3 week window from the baseline interview and randomization, we will audio-record the primary care appointment up to 6 months after the baseline interview, but not after. For the one week follow-up interviews, the allowable Veteran interview range was changed from as early as 5 days from their primary care appointment to as late as 2 weeks prior to their 3-month follow-up; for the 3-month interview the range is from as early as 2.8 months from the primary care appointment to as late as 2 weeks before the 6-month interview; and for their 6-month interview, the ranges is from as early as 5.8 months from the primary care appointment to as late as 9 months from the appointment.

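### The models for recorded visits fix no baseline ACP measure of the Veteran in advance and leave it to a rule triggered by observed imbalance, so some precision is forgone

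*Protocol article*

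**What the plan says.** Under Quantitative assessment of patient activation within clinical encounters, the Protocol article says that activation utterances, ACP topics and discussion time "will be compared between groups using mixed effects models as above with a random intercept for physician". It then adds: "Clinician race/ethnicity, and gender will be included as covariates as these variables are associated with doctor-patient communication". It also plans to control for utterances that suggest the clinician knew the study arm.

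The model referred to is the one under RCT efficacy analysis. That model adjusts for the two blocking factors, health literacy and Veteran race, and "for any predictor variables that differ between study arms at baseline". Baseline comparability is to be assessed with t-tests and chi-square tests on the two groups. The Discussion adds adjustment for the varying time from exposure to the clinic visit.

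Table 2 lists knowledge, self-efficacy and readiness at baseline (for example "Readiness subscales of the ACP Engagement Survey"). It also lists the full ACP Engagement Survey, with its process measures, at baseline and every follow-up. Theoretical foundation says that ACP behaviour is influenced by knowledge, self-efficacy and readiness.

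On numbers, the sample-size text under Secondary outcomes says "we will attempt to audio-record 200 Veterans (100 in each group"), allowing for 25 % Veteran and 25 % clinician refusal. The Discussion limits which visits count: "we will audio-record the primary care appointment up to 6 months after the baseline interview, but not after".

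**The concern.** The survey scores are measured at baseline and at follow-up, so the arm-by-time model uses each Veteran's starting value. Activation is coded from a primary care visit after exposure, and no baseline recording is described. The inherited arm-by-time structure therefore gives this outcome no baseline adjustment of its own. A pre-exposure proxy is the only way to supply one, and the ACP Engagement process score is an obvious candidate for the outcomes concerned with ACP talk.

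The inherited rule brings such a score in only if the arms are seen to differ on it. This has two weaknesses. First, a prognostic covariate narrows the interval even when the arms look balanced, and the rule ignores that benefit. Second, the comparison is described for the two groups as a whole, whereas the recorded subset is about half of those enrolled (200 of 410). A score can balance across 205 per arm and still differ among 100 per arm.

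Veteran activation is a stated secondary hypothesis, and the article treats a difference of a single utterance as clinically relevant. Precision in this subset therefore matters.

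**Working it through.** **1. The subset size reproduces.** The inputs are 350 Veterans retained, or 410 enrolled with 15 % attrition, and two refusal rates of 25 %.
- 350 × 0.75 × 0.75 = 196.9
- 410 × 0.85 × 0.75 × 0.75 = 196.0

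Both are close to the stated 200. The article gives no SD, effect size or power for activation, so no stated figure depends on the covariate choice.

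**2. Reference point (assumed).** Take 100 per arm, two-sided alpha 0.05 (stated for the main sample size, assumed here), and an effect that gives 80 % power without the covariate:
- detectable difference = (1.960 + 0.842) × √(2/100) = 0.396 SD
- for this to equal one utterance, the SD would be 1 / 0.396 = 2.52 utterances. The article does not give the SD.

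**3. Effect of adding the covariate.** Let r be the correlation between the baseline process score and the outcome. It is not in the documents, so a range is shown. In a linear model:
- SE ratio = √(1 − r²)
- effective n per arm = 100 / (1 − r²)
- power = Φ(2.802 / √(1 − r²) − 1.960)

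| r | SE falls by | Effective n per arm | Power |
|---|---|---|---|
| 0.1 | 0.5 % | 101.0 | 80.4 % |
| 0.2 | 2.0 % | 104.2 | 81.6 % |
| 0.3 | 4.6 % | 109.9 | 83.6 % |
| 0.4 | 8.3 % | 119.0 | 86.4 % |
| 0.5 | 13.4 % | 133.3 | 89.9 % |

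Over both arms, 200 / (1 − r²) − 200 gives the equivalent of about 8, 20 or 67 extra recordings for r = 0.2, 0.3 or 0.5. At r = 0 nothing is gained.

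**4. Effect of a chance imbalance.** With 100 per arm, the 95 % limit for a chance difference in the baseline score is 1.960 × √(2/100) = 0.277 SD. The unadjusted estimate in such a sample would shift by r × 0.277, from 0.03 SD (r = 0.1) to 0.14 SD (r = 0.5). This is variation around the right value from one randomisation to another, not a systematic error.

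**5. Limits of the approximation.** Utterances and ACP topics are counts, and the article allows Poisson or negative binomial mixed models. The table is a guide to size for those outcomes, not an exact result.

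**The case against.** The strongest objection is that the section should not be read alone. The clinician covariates are additions to an inherited set that already holds literacy, Veteran race and anything imbalanced at baseline. This stands. A reader might infer that the plan ignores Veteran characteristics, or that protection against chance imbalance is absent. The documents do not support either reading: the protection exists but is conditional and data-driven.

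A reader might also infer that the activation comparison is biased. It is not. Omitting a prognostic covariate from a randomised comparison costs efficiency only. Nor do the documents show that recording depends on arm. A subset stays balanced in expectation unless it does, and if it did, one covariate could not be relied on to repair the damage.

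The benefit is also unproven. The framework links knowledge, self-efficacy and readiness to ACP behaviour, not to how much a Veteran talks in a visit generally, and the article codes overall as well as ACP-specific activation. This stands, and it confines the case mainly to the ACP-specific outcomes.

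Finally, this is a condensed article, and a fuller covariate list may sit in an analysis plan that is not shown. That would answer a complaint about missing detail. Here, however, the article names covariates for this analysis, gives a reason for choosing them, and states the rule for adding others. That stated choice can be improved. The clinician covariates are reasonable and need not be removed.

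**Conclusion.** The point holds as a minor improvement to a stated model. No baseline ACP measure is fixed in advance for outcomes that have no baseline value of their own. The rule that might bring one in depends on observed imbalance, with no check described for the recorded subset.

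The loss is modest at the lower correlations: about 0.5 % to 4.6 % of the standard error for r = 0.1 to 0.3, or 0.4 to 3.6 power points from a base of 80 %. It reaches about 13 % of the standard error, or 9.9 power points, only at r = 0.5, a value for which the documents offer no support. These figures rest on an assumed r, 100 recordings per arm and a linear-model approximation. They do not put the validity of the comparison in doubt.

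**What to change.** In Quantitative assessment of patient activation within clinical encounters, name the baseline ACP Engagement process score (average Likert) as a pre-specified fixed covariate. Do this at least in the models for ACP-specific activation, ACP topics and discussion length, instead of relying on the rule about differences at baseline. The blocking factors are already inherited and need no new wording.

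Use only the baseline score. Table 2 treats these constructs as mediators that the intervention may change, so follow-up values must not enter as covariates. Showing baseline characteristics by arm for the recorded subset would also let readers judge comparability there.

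One caution is worth recording. Randomization procedures has the interviewer look up the assigned arm before the baseline interview, so the score is taken before exposure but not blind to allocation on the interviewer's side. The existing rule for baseline differences shares this limitation.

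The cost is one sentence and one degree of freedom, with no new data collection.

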## Discussion

This is the first study to test the efficacy of a new paradigm of ACP focused on preparing chronically ill older Veterans for communication and medical decision-making as operationalized in the PREPARE website. The development of the PREPARE was based on extensive published formative research in which the community, key stakeholders, and the target population were included in the development of the website. Designed to be easy-to-read and to include culturally competent material, PREPARE is also unique for its user-friendly features such as the use of video modeling of ACP behaviors, tailored and interactive content based on values and decision preferences, and the opportunity to create an action plan for change.

There have been a few logistic challenges to date. Although we attempt to schedule Veteran’s baseline appointment and randomization 1 to 3 weeks prior to their most proximate primary care appointment, this, at times, has been difficult to implement for various reasons. For example, some Veterans reschedule their baseline interview resulting in the intervention occurring within a few days before their clinic visit. Other Veterans or the clinic will cancel a primary care appointment after the baseline interview has occurred resulting in a time frame beyond the three-week ideal. We will adjust for these varying time frames from exposure to the intervention in our analyses. In addition, because the audio-recording occurs at the primary care visit and because several primary outcomes of the study would occur at the primary care visit, we decided to make the primary care visit the date from which all follow-up interviews would be calculated. Because follow-up of the 1-week, 3-month and 6-month interviews within defined time frames was proving challenging, we decided to allow a range of dates that were acceptable. For instance, if a primary care appointment is rescheduled is outside of the ideal 1-3 week window from the baseline interview and randomization, we will audio-record the primary care appointment up to 6 months after the baseline interview, but not after. For the one week follow-up interviews, the allowable Veteran interview range was changed from as early as 5 days from their primary care appointment to as late as 2 weeks prior to their 3-month follow-up; for the 3-month interview the range is from as early as 2.8 months from the primary care appointment to as late as 2 weeks before the 6-month interview; and for their 6-month interview, the ranges is from as early as 5.8 months from the primary care appointment to as late as 9 months from the appointment.

As described in the methods, surrogate recruitment was initially challenging without the ability to obtain verbal consent. However, this was approved by the IRB office part way through the study. Because surrogate contact takes a great deal of time, we have extended the surrogate recruitment date range to up to 6 months after the Veteran had completed their last 6-month follow-up visit. Even so, there have been several surrogates who were interested but never returned the consent materials, or who returned the consent materials but could not be scheduled before the 6-month cut off. We are hoping that verbal consent will make surrogate interviews easier to obtain.

In addition to testing PREPARE, we hope to be able to disseminate the website broadly. By assessing satisfaction with the PREPARE materials and suggestions for implementation and dissemination during the randomized trial phase, should the results be positive, we hope to move from the efficacy trial phase quickly to implementation and dissemination within the VA and the community.

If PREPARE proves efficacious in helping Veterans engage in ACP, communicate their wishes, better prepare themselves and their loved ones for complex medical decision-making, and document their wishes in the medical record, the PREPARE website could prove to be a scalable and effective intervention to improve the care of older Veterans and ensure Veteran’s wishes are honored. Because PREPARE can be used outside of the clinical environment, in future studies it may also save clinicians time and prove to be cost-effective.

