#### Measures related to advance directive and ACP documentation

Standard ACP is measured by the completion of advance directives in the VA electronic medical record. We will assess baseline advance directive completion rates and the date the advance directive was signed as well as ACP discussions. At 6 months (date of the last follow-up interview), we reassess the advance directive completion rate and the date it was signed to determine length of time from study enrollment to documentation. An advance directive for the purposes of this study includes the VA or easy-to-read advance directive, a living will, a durable power of attorney for health care document (DPOAHC), a Physicians Orders of Life Sustaining Treatment form, or other documentation of the patient’s wishes for medical care (code status, such as full code or do not resuscitate or do not intubate orders by a physician).

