#### Measures related to ACP engagement including behavior change process measures and ACP actions

Full ACP engagement is measured by Veteran self-report at baseline, 1 week, 3 months, and 6 months. Based on Social Cognitive Theory and Behavioral Change Theory [18, 19], we included measures to capture theoretical constructs related to contemplation of behavior, planning or intention to act on the behavior, and the behavior itself. If only the action behavior is measured, such as completion of an advance directive, clinically significant movement along the behavior change pathway will be missed. Thus, it is important to ascertain ACP process measures of behavior change (knowledge, contemplation, self-efficacy, and readiness) for several ACP actions in addition to whether they have completed an ACP behavior (Action Measures). These actions include 1) identifying of a surrogate, 2) identifying values and goals, 3) choosing the level of leeway or flexibility in decision-making for the surrogate, 4) and communicating this information with clinicians and surrogate decision makers, and 5) documenting one’s wishes [22]. As Veterans may have had varying degrees of experience with ACP, we assess baseline engagement in ACP within the past 5 years (standardized based on pilot data). We also ask about engagement in ACP since the randomization date, for example, “Within the past one week, 3 or 6 months”, depending upon the follow-up interval.

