## Outcomes and Sample Size Calculations

### Primary outcome

The primary outcome is advance directive documentation in the medical record. This outcome was selected based on prior studies that have shown that advance directive interventions can increase documentation. A meta-analysis demonstrated a pooled effect size of 0.50 (95 % CI; 0.17-0.83) suggesting a positive effect associated with advance directive interventions [36]. One RCT of an ACP workbook in older Veterans also demonstrated an increase in living wills documented from 23 % in controls to 48 % in the intervention group (*P* < .001); and ACP notes from 24 % to 47 % (*P* < .001) [37]. Consistent with results from prior studies, our pilot study showed that a literacy appropriate advance directive doubled completion rates from baseline [12]. From SFVAMC administrative data, 11 % of the potential study sample had an advance directive in their medical record. We assume that after being included in the study, the control group may have an advance directive documentation rate of 15 %. If we assume doubling of the percent of ACP discussion notes between groups (what we consider clinically significant), a sample size of 350, or 175 in each arm, will afford us 92 % power with a two-tailed alpha of 0.05 to detect an elevation in rate of advance directive documentation from 15 % in controls to 30 % in the PREPARE group and 80 % power to detect a difference of 15 % in controls versus 27 % in the PREPARE group. After accounting for an estimated 15 % attrition rate, including death at 6 months (based on prior work) [12], our recruitment target is 410 Veterans or 205 in each arm.

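### The chart-based primary outcome has no fixed time from randomisation: it is read at the last interview, which is timed from a movable primary care visit after randomisation

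*Protocol article*

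**What the plan says.** All places are in the protocol article.

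- **Outcome and reading date.** The Primary outcome section names advance directive documentation in the medical record. The section on measures of advance directive and ACP documentation says "At 6 months (date of the last follow-up interview), we reassess the advance directive completion rate". It also records the signing date, so that time from enrolment to documentation can be measured.
- **Anchor of the interviews.** The Discussion says "we decided to make the primary care visit the date from which all follow-up interviews would be calculated". It allows the 6-month interview from "as early as 5.8 months from the primary care appointment to as late as 9 months from the appointment".
- **Gap before the visit.** The section on recruitment by phone aims for a baseline interview 1 to 3 weeks before the visit. The Discussion reports departures in both directions. Some baseline interviews were rescheduled, "resulting in the intervention occurring within a few days before their clinic visit". Some visits were cancelled after baseline, which took the gap beyond three weeks. For moved visits it says "we will audio-record the primary care appointment up to 6 months after the baseline interview, but not after". It promises adjustment for these varying times and gives no method.
- **Survey recall.** The section on ACP engagement measures says "We also ask about engagement in ACP since the randomization date", and gives as examples recall over the past week, 3 months or 6 months.
- **Attrition.** The Primary outcome section sets the recruitment target thus: "After accounting for an estimated 15 % attrition rate, including death at 6 months", 350 becomes 410.

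**The concern.** An outcome that accumulates needs the same start and the same end for everyone. Here the end depends on two events that come after allocation: when the primary care visit takes place, and when within a window of more than three months the last interview is held. The resulting 6-month rate mixes readings at different times after randomisation. It is no longer clearly the quantity for which the trial was sized.

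If visit or interview timing differed by arm, one arm would have longer to accumulate documents and the comparison would be biased. The pre-visit reminder calls differ in content between arms (Intervention and control conditions), so equal timing cannot simply be assumed.

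The promised adjustment does not settle this. It covers the gap from exposure, not the width of the interview window. Where a visit is moved after allocation, it conditions on a post-randomisation quantity. It also gives no date to a Veteran who has no visit or no last interview.

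Finally, the article uses three time origins: enrolment for time to documentation, randomisation for survey recall, and the visit for interviews.

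**Working it through.** **1. The plan's own figures.** Inputs from the Primary outcome section: 175 per arm, two-sided alpha 0.05, 15% v 30% and 15% v 27%. Power = Φ{[d − 1.96·√(2p̄(1−p̄)/n)] / √[(p₁(1−p₁)+p₂(1−p₂))/n]}, where p̄ is the mean of the two rates.

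- 15% v 30%, n = 175: (0.15 − 1.96×0.04464)/0.04392 = 1.423, power 92.3% (stated 92%).
- 15% v 27%, n = 175: (0.12 − 1.96×0.04354)/0.04307 = 0.805, power 79.0% (stated 80%).
- 350/0.85 = 412 (stated 410).

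These reproduce. The sample size is not the fault here.

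**2. When the chart is read.** Time from randomisation = gap from baseline to visit + 5.8 to 9 months. Baseline interview and randomisation are treated as the same day, and 1 month = 30.44 days.

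| Gap to visit | Earliest reading (months) | Latest reading (months) |
|---|---|---|
| 3 days (assumed value for a few days) | 0.10 + 5.8 = 5.9 | 0.10 + 9 = 9.1 |
| 1 week | 0.23 + 5.8 = 6.0 | 0.23 + 9 = 9.2 |
| 3 weeks | 0.69 + 5.8 = 6.5 | 0.69 + 9 = 9.7 |
| 6 months (audio-recording limit, assumed to limit the visit) | 6 + 5.8 = 11.8 | 6 + 9 = 15 |

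**3. How far the reading date can move the rate.** The article gives no accrual rate, so this is a range under assumption. If nothing were documented after 6 months, the rates would stay at 15% and 30%. If documentation came at a constant hazard from randomisation, giving 15% and 30% at 6 months, the proportion at t months would be 1 − 0.85^(t/6) and 1 − 0.70^(t/6):

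- 9 months: 21.6% and 41.4%.
- 15 months: 33.4% and 59.0%.

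The constant hazard ignores directives already on file, so it serves only as an illustration of the upper side.

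**4. Veterans with no reading date.** If the charts of drop-outs would otherwise be left out, and if the planned rates hold in all randomised Veterans, using 205 per arm gives:

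- 15% v 30%: (0.15 − 1.96×0.04125)/0.04057 = 1.70, power 95.6% against 92.3%.
- 15% v 27%: (0.12 − 1.96×0.04023)/0.03979 = 1.03, power 84.9% against 79.0%.

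**5. Survey recall.** The 1-week interview is allowed from 5 days after the visit. With a visit at least 1 week after randomisation, that is 7 + 5 = 12 days or more. A recall of one week would not reach back to randomisation.

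**The case against.** The visit is a reasoned anchor: the audio-recording and several outcomes occur there, and scheduling aims to standardise the time from exposure to visit. Scheduling and windows are the same in both arms, both arms receive a reminder call, and follow-up interviewers are blinded. Timing that varies within arms but is balanced between them creates no spurious difference. Part of the gap is also settled before allocation, as when a baseline interview is rescheduled. All of this stands. It means that bias between arms is a possibility, not a finding, and that the anchor suits the interviews. It does not make the visit a good clock for a dated record.

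A reader might go further in several directions that the article does not support:

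- **That the outcome is lost for drop-outs and intention to treat is broken.** No section says that their charts go unread. The 15% is an ordinary inflation of the sample size, applied to the survey outcomes too, and the last interview could mean the last one attended. On that reading, however, a Veteran last seen at 1 week would have the chart read then, which makes observation time more uneven.
- **That readings commonly reach 15 months.** That figure adds two maxima and borrows a limit stated for audio-recording only.
- **That 11% rising to 15% is an accrual rate.** The 11% is prevalence in administrative data for the potential sample, and the 15% is an assumed control rate once in the study. Neither gives a rate per month.
- **That the survey misses early actions.** The stated recall origin is randomisation, the windows are examples, and the questionnaire is not shown. This is an inconsistency of wording.

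The recorded signing date is a real mitigation, because it allows a fixed window to be built for directives. The article does not say that this will be done.

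**Conclusion.** The point holds as a fault in the definition of the primary outcome. Followed as written, the chart is read about 6.0 to 9.7 months after randomisation when the visit falls in its intended window. It is read later when the visit is delayed, with about 15 months as an extreme that rests on the assumption about the audio-recording limit. The measured rate depends on that date to an extent that the article does not allow one to fix: from no change to about 7 points in controls (21.6% against 15%) for a 9-month reading under a constant hazard.

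Bias between arms would follow only if timing differed by arm, which the article neither shows nor prevents. Veterans without a visit or last interview lack a defined reading date; whether their data would be dropped is not stated. The gain in power from reading every chart is conditional for the same reason. The stated power is not in error on this point.

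**What to change.** - Define the primary outcome as documentation dated from randomisation to one fixed time, for every randomised Veteran, whether or not the visit or any interview took place. Count documents dated before death.
- Choose the time, for example 6 or 9 months, before any unblinded comparison. Six months keeps the stated label; nine leaves more room for delayed visits.
- Do not rely on adjustment for the delay to the visit in the primary analysis.
- Reconcile the documentation section, the engagement section and the Discussion on the time origin. State the survey recall as since randomisation for interviews still to be done, and drop the example of the past week.

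The cost is a change of wording and one extraction of dated entries for 410 Veterans at one centre. Signing dates are already collected for directives. The article does not say that dates are collected for notes and code status orders, so these may have to be added. The small drawback is that chart and interview times will no longer coincide; the interviews can keep the visit as their anchor.
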